## Abstract

**Background:**

There are inequities in health status associated with ethnicity, which may limit older foreign-born persons’ ability to age optimally. Health promotion for older persons who have experienced migration is thus an area of public health importance. However, since research related to this issue is very limited, the study ‘Promoting Aging Migrants’ Capabilities’ was initiated to improve our understanding. The study aims to implement and evaluate a linguistically adapted, evidence-based, health-promoting intervention with a person-centred approach for two of the largest groups of aging persons who have migrated to Sweden: persons from Finland and persons from the Balkan Peninsula.

**Methods/Design:**

This study has a descriptive, analytical, and experimental design. It is both a randomised controlled trial and an implementation study, containing the collection and analysis of both qualitative and quantitative data. The setting is an urban district in a medium-sized Swedish city with a high proportion of persons who were born abroad and whose socio-economic status is low. The intervention comprises four group meetings (‘senior meetings’) and one follow-up home visit made by a multi-professional team. For the randomised controlled trial, the plan is to recruit at least 130 community-dwelling persons 70 years or older from the target group. Additional persons from involved organisations will participate in the study of the implementation. Both the intervention effects in the target group (outcome) and the results of the implementation process (output) will be evaluated.

**Discussion:**

The results of this forthcoming randomised controlled trial and implementation study may be useful for optimising implementation of person-centred, health-promoting initiatives for older persons who have experienced migration. It is also hoped that this combined study will show that the capabilities for optimal aging among older persons born in Finland and the Balkan countries can be improved in the Swedish healthcare context.

**Trial registration:**

The trial was registered at ClinicalTrials.gov April 10, 2013, identifier: NCT01841853.

## Background

Optimal aging may be defined as the capacity to function across many domains (physical, functional, cognitive, emotional, social, and spiritual) to one’s own satisfaction and despite one’s medical conditions [1]. The realization of optimal aging is of vital importance since the proportion of older persons in the population is expected to increase in both Sweden and the rest of Europe [2,3]. Today, persons above 67 years of age constitute about 17% of the Swedish population and are expected to constitute 21% by the year 2020 [3]. Additionally, the number of aging persons who migrate from one country of residence to another is rising [4]. Persons who have migrated to Sweden constitute 13% of the population over 65 years of age, and this figure is expected to increase to 15% by 2020 [3]. According to the parliamentary bill on research [5], the aging population will pose challenges to Swedish health and welfare services, with increased costs for care and healthcare. However, the parliamentary bill also points out that research on aging and health can contribute to great gains, both health-wise and economically, for individuals as well as for society as a whole. In addition, it stresses that the focus should be on using evidence-based knowledge, health promotion, interdisciplinarity, and a person-centred approach [5]. In view of the above information, it is clear that research on the health of older persons who have experienced migration is an area of utmost importance.

The National Board of Health and Welfare in Sweden emphasises that healthcare should systematically integrate and target specific health-promoting and disease-preventive interventions daily to provide equal healthcare for the whole Swedish population [6]. However, aging persons might not have equal opportunities to enjoy good health because of factors at an individual (micro), group (meso), or societal (macro) level, which can limit a person’s capability for optimal aging. Individual factors (e.g. physical health and cognition), group factors (e.g. family and community), and societal factors (e.g. laws and healthcare services) can at any given time form the basis for an individual’s capability set, i.e. what an individual actually can or cannot do [7]. For instance, we know today that there are inequities in health status associated with ethnicity [8], and persons who have migrated to Sweden run a greater risk of developing cardiovascular diseases and mental illness than their native-born counterparts [9,10]. In addition, conceptions of health and aging among persons who were born abroad may be shaped by the process of migration, and thus differ from the ones held by native Swedes [11]. Hence, based on a growing body of knowledge that suggests that age-related decline can be delayed [12], health promotion for older persons could be a strategy for achieving optimal aging. Health promotion is a process that enables people to increase control over and improve their health [13]. It aims to empower individuals by strengthening their capabilities to enhance accomplishment in everyday living and self-efficacy [14]. In targeting equality in the Swedish healthcare context, it is essential to design and evaluate health-promoting initiatives for older persons born abroad.

The persons who would probably benefit most from a health-promoting programme are those who have not yet reached any restrictions in activity level [15], are pre-frail (having less than three of five physical frailty criteria [16]), or are at risk of frailty [17,18]. Frailty is a state of decreased reserve resistance to stressors as a result of cumulative decline across multiple physiological systems, which cause vulnerability to different outcomes [19]. The prevalence of frailty increases with age and is associated with an elevated risk of adverse health outcomes, such as dependence, falls, hospitalisation, institutionalisation, and mortality [19,20]. Older persons who have experienced migration are often excluded from research studies because of linguistic and other barriers [21], limiting the knowledge of healthcare needs within these groups. In addition, they can be at double jeopardy for developing frailty, and are often described as a vulnerable group exposed to isolation and mental illness, as well as having language problems when seeking healthcare services. However, older persons who were born abroad are a heterogeneous group of people, originating from many different countries and with different healthcare needs. Therefore, a person-centred approach to health-promotion, aiming to recognise each person’s different and constantly changing experiences and requirements, is desirable. It can ensure that the persons concerned are able to influence their own healthcare processes, a factor that has been shown to have a significant impact on older persons’ experiences of the overall quality of care [22]. Person-centredness entails shared decision-making, meaning that all decisions concerning care, treatment, rehabilitation, and health-promoting activities ought to be taken in partnership [23].

A literature review and meta-analysis of health-promoting programmes targeting aging persons who have culturally and linguistically diverse backgrounds have shown that research in this area is very limited ([name], [name], [name]: Unpublished observations). To our knowledge, there is no health-promoting programme that integrates a person-centred approach for older persons who were born abroad and are at risk of developing frailty. However, the continuing analyses of a recently completed randomised controlled trial (RCT), ‘Elderly Persons in the Risk Zone’ [24], is providing growing evidence that a health-promoting programme targeting pre-frail persons 80 years and older can achieve good results. Two different interventions have been evaluated: 1) a single preventive home visit and 2) a group-based intervention with four senior meetings and one follow-up home visit. The senior meetings show the most advantageous results, including delayed deterioration in self-rated health, dependence in activities of daily life (ADL), and morbidity [25-27]. Further, qualitative interviews show that this intervention is perceived as a key to action, supporting self-change towards healthier life style choices [28]. The hypothesis in ‘Elderly Persons in the Risk Zone’ was that if an intervention is conducted when older persons are pre-frail, then it is possible to prevent or delay deterioration in health. This hypothesis, and the design and content used in the evidence-based ‘senior meetings’ intervention (with minor adaptation), ought to apply to older pre-frail persons born abroad.

Consequently, the present study, ‘Promoting Aging Migrants’ Capabilities’, was designed, aiming to implement and evaluate the aforementioned evidence-based, health-promoting intervention (‘senior meetings’) with a person-centred approach for two of the largest groups of aging persons who have migrated to Sweden; persons from Finland and persons from the Balkan Peninsula [29]. In preparation for the study, interviews were held with older persons who have experienced migration, and focus groups were conducted with personnel working in the targeted urban district [30,31]. Additionally, collaboration was initiated with reference groups of older persons from the target group living in the city in question to gather knowledge and provide guidance on how to adapt the original intervention protocol to older persons in the target population.

The implementation of a new method or approach in a healthcare organisation may face resistance or various difficulties; it is often not a simple and straightforward process. Therefore, various factors need to be studied and assessed, such as usability, adaptations, barriers, fidelity, and anticipated impact. To broaden the perspective, the present study will evaluate both intervention effects in the target group (outcome) and the results of the implementation process (output). To fully understand the intervention and implementation process, a mix of methods will be used. This approach will hopefully contribute to improving the capabilities of older persons who are born abroad to age optimally in the Swedish welfare context. This paper presents the design of the Promoting Aging Migrants’ Capabilities Study, an RCT as well as an implementation study, which was written in accordance with the SPIRIT guidelines for study protocol content [32,33], and the CONSORT recommendations for reporting pragmatic RCTs [34].

### Aims and research questions for the study

The overall aim of the Promoting Aging Migrants’ Capabilities Study is to implement the evidence-based ‘senior meetings’ intervention among older persons who have migrated to Sweden, a person-centred approach to health promotion to support optimal aging in the Swedish context. The study aims to prove the following two hypotheses:If a health-promoting programme is introduced when older persons who were born abroad are pre-frail, it is possible to prevent or delay deterioration in health (i.e. dependence in ADL, self-rated health) and life satisfaction.The design and content of the evidence-based senior meetings can be used in the context of older persons who have migrated to Sweden.

Specifically, the study addresses the following research questions:Can a person-centred, health-promoting programme for older persons who were born abroad:Prevent decline in physical function, activity performance, leisure pursuits, and life satisfaction?Be a supportive factor in the social network, and if so, how?Have an impact on the consumption of care?Could the design and content of the evidence-based senior meetings:Be adapted for older persons who have migrated to Sweden, and if so, how?Support self-change behaviour, and if so, how?Be implemented with high fidelity?How do older persons who were born abroad, and the personnel in the targeted urban district, experience the programme, its significance, and importance for health?

## Methods/Design

The Promoting Aging Migrants’ Capabilities Study has a descriptive, analytical, and experimental design. It is both an RCT and an implementation study, containing the collection and analysis of both qualitative and quantitative data. The combination of quantitative and qualitative methods in the study will best answer the research questions, as well as taking advantage of the strengths of both methodological approaches [35]. The participants in the RCT are randomised into two study arms (one intervention and one control group), and outcomes at 6- and 12-month follow-ups will be analysed. A pilot study has been conducted before the full-scale RCT to assess the feasibility of the programme, and has guided the final protocol ([name], [name], [name]: Unpublished observations). The implementation part of the study has a case study design [36], and will be carried out alongside the RCT. In addition, individual in-depth interviews of both participants and personnel will be conducted to determine the perceived effect and significance of the programme.

### Study context

Activities in care and healthcare for older persons in Sweden include a number of actors that interact in different ways. Medical care is predominantly performed in the public sector (80%), and healthcare costs are financed mainly through taxes and government grants. Cities and municipalities are responsible for services for older persons. The aim of these services is to ensure that older persons are able to live as independently as possible in their own homes. When older persons are no longer able to manage daily life independently, they can apply for assistance from the municipal home help service. The extent of such support is subject to an assessment of needs; it may include meals on wheels, help with cleaning and shopping, assistance with personal care, safety alarms, transportation services, and healthcare.

The location of the Promoting Aging Migrants’ Capabilities Study is an urban district in a medium-sized city in the western part of Sweden. The urban district is situated outside the city centre, but within city limits, with the majority of living accommodations consisting of blocks of flats. In 2013, the total population was 49,920 persons of which 5,491 (11%) were 65 years or older [37]. Fifty per cent of all inhabitants in the urban district were born in countries outside Sweden (other Nordic countries as well as countries within and outside Europe). The most frequently represented countries of birth, regardless of the person’s age, were in descending order: Iraq, Iran, Finland, Bosnia-Herzegovina, and the former Yugoslavia. The latter three were, however, dominant countries of birth for persons 65 years or older. There are no available statistics of causes of immigration for residents in the targeted urban district, but these causes would likely mirror those for Sweden as a whole: work/studies, escape from war, family ties, and other reasons. In 2012, the general education level and income level of residents in the urban district were lower, and the sickness rate higher, than in the population of the city as a whole [37].

### Intervention

The intervention implemented in the Promoting Aging Migrants’ Capabilities Study is the evidence- and group-based, health-promoting ‘senior meetings’ programme. The main purpose of the senior meetings is to facilitate discussion of the aging process and to provide tools and strategies to enable participants to solve various problems that may arise at home so that they can remain living at home in a safe and secure way. A booklet containing different aspects of health self-management (e.g. physical activity, medication, nutrition, assistive devices, adaptation of housing, memory, quality of life) is used as material for group discussions [38]. The senior meetings also inform participants of what the municipality provides in the form of local meeting places, activities run by local associations, physical training for seniors, walking groups, and possibilities of offering or accepting help on a voluntary basis. Available help and support offered by the municipality are addressed and discussed. Identification of risks for falls and advice on how to prevent them are also included. For an overview of the chapters in the booklet and the profession responsible for each section, see Table 1.

**Table 1 Tab1:** **Themes from the booklet used in senior meetings in the promoting aging migrants’ capabilities study**

**Themes from the booklet**	**Principal professional** *****
Aging	PT
Physical activity helps keep you physically fit	PT
Food is a prerequisite for health	PT
You can take care of problems with your health	RN
How to use medicines	RN
To cope with everyday life	OT
You do not need to feel insecure	OT
Technology in everyday life	OT
Will I lose my memory?	OT
Life events and quality of life during aging	SW
Anyone who needs help can get help	SW

*Physiotherapist (PT), registered nurse (RN), occupational therapist (OT), and social worker (SW).

The senior meetings are conducted by an operative group consisting of professionals employed in the urban district: an occupational therapist, a registered nurse, a physiotherapist, and a social worker. All professionals receive education and training on the programme content, and on leading groups prior to study commencement. The programme comprises four weekly senior meetings in small groups (four to six participants), in addition to an individual follow-up home visit two to three weeks after the last senior meeting. Having groups enables the possibility of peer education with participants learning from each other [39], and a person-centred approach increases the possibilities for participants to be seen as experts on their own situation [40]. Respect for the participant and his/her values and giving each participant the opportunity to maintain and develop his/her control over his/her own everyday activities, is essential in the meetings.

Some minor but important adaptations of the original senior meetings protocol [24] were made when designing the Promoting Aging Migrants’ Capabilities Study. First, since several languages were to be involved, the study adopted a bilingual approach, where all written participant material is printed in Swedish and the participants’ mother tongue. Recordings of material to compact disc (CD) in participants’ preferred languages are also available. If needed and sought, interpreters are engaged in study activities. Second, based on the dialogue with the reference groups, a section covering how to handle post-traumatic stress in everyday life was added to the booklet. Third, when the booklet was revised, some smaller sections that were deemed redundant by personnel in the urban district were removed to reduce the text. Finally, to further clarify and consolidate the person-centred approach, seminars based on scientific literature and dialogue were held jointly with the operative group and research group.

In this intervention, the risk of causing adverse events is judged to be low. However, any unforeseen harm will be documented by the operative group and reported to both the research group and the steering committee. When necessary, adequate responsive actions, for instance referral to medical care, will also be taken. To promote comparability of RCT study groups, concomitant care and interventions during participation in the study will be avoided as much as possible. Participants randomised to the control group will not be included in the intervention, but will receive conventional care on their own initiative, as well as undergoing study baseline and follow-up assessments.

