**Planned flow of participants in the Promoting Aging Migrants’ Capabilities Study.**

The invitation process and data collection are conducted by trained research assistants and conducted in the language preferred by the participant. The standardised baseline assessment comprises an interview, measurements, and observation. Follow-up data, identical to the baseline assessment except for demographics, will be collected in both groups at 6- and 12 months after the intervention. The complete data collection form, as well as consent and participant information forms, can be retrieved by contacting the first author (SG) or last author ([name]). In addition, information on reasons for any non-adherence (e.g. discontinuation of intervention) and non-retention (i.e. consent withdrawn or lost to follow-up) will be collected. Data from municipal registers will also be obtained and used to study care consumption.

The recruitment of participants began in autumn 2012 and is planned to be completed by the end of December 2014. The intervention began at the same time as the inclusion, and will be completed no later than 6 months after the last inclusion. The 12-months follow-up will be completed in January 2016. A detailed study timeline is shown in Table 4.

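### Recording of unforeseen harm is assigned to the staff who deliver the programme, with no equivalent route stated for controls or for later follow-up, so these reports cannot be compared between arms

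*Protocol article*

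**What the plan says.** The Intervention section of the protocol article opens its statement on harm with a judgement: "In this intervention, the risk of causing adverse events is judged to be low". It then gives the recording rule: "any unforeseen harm will be documented by the operative group", with reports passed on to the research group and steering committee. Referral to medical care follows where needed.

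The same section identifies the recorders: "The senior meetings are conducted by an operative group consisting of professionals employed in the urban district". It also sets the length of their scheduled contact: "The programme comprises four weekly senior meetings in small groups (four to six participants), in addition to an individual follow-up home visit", with the home visit two to three weeks after the last meeting.

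For the other arm it says: "Participants randomised to the control group will not be included in the intervention, but will receive conventional care on their own initiative". Controls do have the baseline and follow-up assessments. The section on recruitment, participant timeline and randomisation says who does these: "The invitation process and data collection are conducted by trained research assistants". The follow-up assessment covers both groups at 6 and 12 months.

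The low-risk judgement is used elsewhere. The Data management section gives minimal risk as one reason for having no data monitoring committee, and the section on ethical considerations calls the risk small relative to the benefit.

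**The concern.** The one stated route for unforeseen harm depends on people who meet one arm, under the programme, for a few weeks. No post-randomisation contact between the operative group and controls is described. The research assistants meet both arms on the same schedule but are given no task of this kind.

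Two things are at stake. First, if the reports were later set out by arm, a difference could reflect who was watching rather than what happened. Second, a low number of reports would say little about whether the programme is safe, because most of the follow-up has no stated recorder in either arm. That matters because the section on ethical considerations plans to offer the programme to controls if it proves effective.

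That section also names a burden that falls on both arms: participants may find the assessments tiring. This arises where the research assistants are present and the operative group is not. The section gives a response (a shorter visit or a reduced form) but does not say that the event is recorded.

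**Working it through.** The article gives no harm rate or harm count, so there is no figure of the plan's own to reproduce. The check is to see who observes each arm and when.

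**Who observes whom after randomisation**

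| Period | Intervention arm | Control arm |
|---|---|---|
| Senior meetings and home visit | Operative group, which has the recording duty | No described contact with the operative group |
| Home visit to 6 months | No stated recorder | No stated recorder |
| 6- and 12-month assessments | Research assistants, no stated harm duty | Research assistants, no stated harm duty |

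The Abstract attributes the home visit to a multi-professional team. I take this to be the operative group. In the third recruitment wave, interested persons may contact the operative group, but that is before randomisation.

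**How much of the follow-up the route covers in the intervention arm**

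- Four weekly meetings: 3 weeks from first to last.
- Home visit: 2 to 3 weeks later.
- Scheduled contact: 3 + 2 = 5 weeks to 3 + 3 = 6 weeks.

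The recruitment section times follow-up from the intervention. On that reading, with 12 months taken as 52 weeks, the share covered is 5/(5 + 52) = 8.8% to 6/(6 + 52) = 10.3%. The section on dissemination policy speaks of interviews one year after randomisation. On that reading the share is 5/52 = 9.6% to 6/52 = 11.5%. Either way it is about one tenth. In the control arm the scheduled share is zero.

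**What that means for numbers**

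Assume 65 per arm (from the Power calculation section), a risk of unforeseen events over the whole period of 5%, 10% or 20%, and events spread evenly over time. The risks and the even spread are my assumptions. Expected events in the intervention arm are 65 × risk, and those falling within the contact window are that number × 0.088 to 0.115.

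| Assumed risk | Expected events | Within the window |
|---|---|---|
| 5% | 3.25 | 0.29 to 0.37 |
| 10% | 6.5 | 0.57 to 0.75 |
| 20% | 13 | 1.14 to 1.50 |

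Staff could still hear of later events informally, so this is coverage by scheduled contact and not a forecast of reports.

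**Why the imbalance between arms cannot be sized**

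With equal true risk p and n per arm, the expected recorded counts are n·p·cI and n·p·cC, where cI and cC are the proportions of events captured in the intervention and control arms. Their ratio is cI/cC. The article fixes neither proportion. More contact would raise cI. Staff recording harms of a programme that they deliver themselves might lower it. The direction is therefore not certain either.

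**What is collected symmetrically**

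Table 3 schedules falls, fear of falls, symptoms, depression, weight loss, cognition, self-rated health and register-based healthcare consumption at baseline, 6 and 12 months. The recruitment section says that follow-up is collected in both groups. It also collects reasons for non-retention, with no restriction to one arm.

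**The case against.** The strongest reply is that the rule concerns harm caused by the programme. Controls do not receive it, so the delivery staff are the natural people to notice such harm and pass it on. The Statistical analyses section plans no count, rate or test of unforeseen harms by arm. This stands: no stated analysis is biased.

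A reader might infer that every harm comparison in the trial is one-sided. The documents do not support that. Falls, symptoms and depression are measured alike in both arms, though by unblinded assessors, and register data on healthcare consumption do not depend on who meets the participant.

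A reader might also infer that the operative group is the sole recorder and never sees controls. The article names one route and excludes no other. The group's members are district employees, and the article does not say whether they also meet controls in conventional care.

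Finally, this is a journal article, and the complete data collection form is available on request but not shown. It may already hold an open question on harm. This limits the point but does not remove it. The article states who records, and its Discussion claims to address all the minimum items of the SPIRIT guideline, so the assignment is a stated rule and not a detail left out.

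**Conclusion.** The point holds in a limited form and is minor. The stated route for unforeseen harm runs through the programme staff, with no equivalent stated for controls or for either arm after the home visit. Its scheduled contact covers about one tenth of the period to the 12-month assessment in one arm and none in the other. Reports from it should not be compared between arms, and a small number of them should not be taken as evidence of low risk. Between-arm evidence on harm has to come from the symmetric secondary outcomes.

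It would go too far to say that the trial will make the programme look harmful, or to attach a p-value to that. This would need an event rate and capture proportions that the article does not give, and near-complete capture in the intervention arm, which does not fit with contact ending after a few weeks.

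The conclusion assumes that the home visit is made by the operative group and that no further harm procedure sits in the documents not shown. The sample size is unaffected.

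**What to change.** In the Intervention section, add that the research assistants ask one identical open question on unforeseen harm in both arms at the existing 6- and 12-month assessments. Report the answers by randomised arm. Keep the operative group's reporting line to the research group and steering committee, and list its reports separately as observations from the intervention arm only. If the data collection form already contains such a question, it is enough to say so in that section.

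This needs no new visits or staff. The costs are slightly longer interviews, in a study that already notes that the assessments may be tiring, and answers still taken by unblinded assessors. The question equalises the opportunity to report but does not remove reporting bias.
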